**Participants who completed the program**
Number and proportion of participants who completed the program—via log sheet
**Proportion of dropouts (exit program prematurely) and reasons**
Number and proportion of dropouts and reasons—via log sheet
**Actual costs of the screening program**
Operational costs (eg, electrocardiogram devices, subscription fee to Kardia monitoring portal, and mail postages) recorded and verified using invoices and receiptsCosts of personnel involved in interpreting electrocardiograms computed based on their hourly wage and the time they spent in their roles in this program—data collected prospectively and throughout program implementation
**Agreement in electrocardiogram interpretations**
Number of consultations and percentages of agreement between the monitoring personnel and cardiologists in clarifying uncertain electrocardiogram abnormalities—logs of all interactions
**Usability assessment at the 12th month**
Responses to the Usability questionnaire will be assessed by 5-point Likert scale—via self-report questionnaires (Multimedia Appendix 1)
**Participant acceptability and barriers to and enablers of implementation**
In-depth one-on-one interview with participants (Multimedia Appendix 1) and general practitioners (Multimedia Appendix 2)Thematic analysis
**Impact of frailty on feasibility assessments and the outcomes**
Frailty assessed by the 5-item FRAIL (Fatigue, Resistance, Ambulation, Illnesses, and Loss of Weight) scale (Multimedia Appendix 1)

### Ethics and Dissemination

This study was approved by the human research ethics committee of the University of Sydney (reference number 2020/680). The study is conducted in full conformance with principles of the International Committee on Harmonization of Good Clinical Practice and *Declaration of Helsinki* Good Clinical Practice guidelines and within the laws and regulations of the Australian National Health and Medical Research Council.

## Results

This study was funded by a National Heart Foundation Vanguard grant awarded in October 2019. The study was approved by the human research ethics committee of the University of Sydney in November 2020. The first participant was enrolled in May 2021. As of December 2021, a total of 112 participants have been enrolled. Data analysis and results are expected to be published in December 2023.

## Discussion

### Anticipated Strengths

This patient-led AF screening in the community is different from clinician-led opportunistic screening. In this model of screening, participants are trained and empowered to self-record ECGs instead of awaiting clinicians to screen them opportunistically. The centralized remote monitoring team will facilitate patient access to see their GPs.

Drawing on the strengths of quantitative and qualitative methodologies [45], this study will provide evidence for AF detection rates, participant satisfaction, and feasibility of implementing this program using a telephone, a video interface, and the internet for older people, including people who are frail, with the potential to extend to other vulnerable groups such as people with disabilities, people who are socially isolated or because of the COVID-19 pandemic lockdown, and those who live in remote areas.

Participant satisfaction scores often reflect the convergence and gap between participant expectations and actual experiences [46], and satisfaction scores also measure how well the intervention was received by participants [31]; hence, satisfaction is a commonly evaluated outcome in clinical trials [46]. Nonetheless, satisfaction scores would not provide insights into participant experiences, which provide contextualized feedback to improve the screening program. We complement this with in-depth one-on-one semistructured interviews with participants and GPs to explore their insights on barriers and enablers.

This is a prospective RCT design. The waitlist-controlled design provides equitable access to all participants in a mass screening strategy. It is a simple, acceptable, and noninvasive screening strategy that can be implemented regardless of geographical location. Our novel approach in promoting patient-empowered self-screening integrated with a clinician-coordinated centralized system will provide patients with integrated care that facilitates access to GPs and specialist services. Patients will receive training to use the device, and they will be reminded to perform their routine ECGs if they have not done so for 3 consecutive days. This type of interaction and reminder system has been proven to yield positive health outcomes such as engagement in positive health behaviors [47]. Performing self-screening could raise awareness of self-care and improve patient confidence in self-care, which is a form of patient empowerment that is promoted by the World Health Organization [24].

We anticipate that this study will provide data on whether implementation of this type of community-based model of care is feasible and acceptable to patients and health providers in the community. At study completion, the results will be shared with the Heart Foundation (study funder), policy makers, health providers, consumers, and other stakeholders. Access to ECG monitoring devices for future screening programs is dependent on feasibility from a cost perspective, as well as aspects of whether this would be a barrier to implementation. We will conduct a qualitative analysis to understand participants’ perceptions of the value of the monitoring device to their well-being, as well as the affordability of the device.

### Anticipated Research Outcomes and Impacts on Clinical Practice and Policy

This study will provide information on the usability of and costs associated with AF mass screening in Australian people aged ≥75 years. It will also provide evidence of AF incidence in older people in Australia. This can potentially facilitate the development of a national screening program for AF in older people and people who are frail.

Screening for AF is more likely to occur in the community or general practice setting than in the hospital setting. It took an average of 10.6 minutes to acquire a 12-lead ECG in a general practice setting (including the time preparing the patient for ECG acquisition and placing the electrodes correctly on the patient) [48]. In contrast, this patient-empowered self-screening potentially reduces time constraints faced by clinicians as patients are empowered to self-record ECGs in the community rather than clinicians spending the additional time acquiring ECGs opportunistically in a busy clinical setting. In this program, GPs can access help from the participating cardiology team to confirm the diagnosis and facilitate appropriate management of new AF if necessary. This could enhance access and interaction between GPs and cardiologists in providing integrated care to patients to achieve better health outcomes.

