**Results:**

This study will establish the feasibility and effectiveness of implementing the intervention in this patient population. The primary clinical outcome is the AF detection rate, and the primary feasibility outcome is the patient satisfaction score. Other outcomes include appropriate use of anticoagulant therapy, participant recruitment rate, program engagement (eg, frequency of ECG transmission), agreement in ECG interpretation between the device automatic algorithm and clinicians, the proportion of participants who complete the trial and number of dropouts, and the impact of frailty on feasibility and outcomes. We will conduct a qualitative evaluation to examine the barriers to and acceptability and enablers of implementation. Ethics approval was obtained from the human research ethics committee at the University of Sydney (project number 2020/680). The results will be disseminated via conventional scientiﬁc forums, including peer-reviewed publications and presentations at national and international conferences.

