## Introduction

### Background

The prevalence and incidence of atrial fibrillation (AF) increase with age and is common among older people [1-4]. A recent study estimated that the global prevalence of AF is 59.7 million [4]. Approximately 70% of individuals with AF are aged between 65 and 85 years [5]. AF has been reported to account for 36% of all ischemic strokes, of which 85% are inadequately anticoagulated [6]. If AF is detected early and managed with appropriate anticoagulation therapy, the stroke risk and subsequent stroke-related disability and mortality can be reduced significantly [7]. Unfortunately, it was estimated that 1% of the general population and 1.4% of people aged ≥65 years were living with undiagnosed AF, as reported in a systematic review that combined data from 30 cross-sectional studies (n=122,571) [8]. Hence, the opportunity for anticoagulation therapy to reduce stroke risk for these patients is missed.

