### Study Population

Our target population involves older people living independently in the community outside of a hospital, nursing home, or similar institutional residence. The inclusion criteria are as follows: community-dwelling people aged ≥75 years, having a smartphone or electronic device that can operate the AliveCor Kardia mobile app, and being able to understand instructions in English. Individuals with the following conditions will be excluded: previously confirmed diagnosis of AF, having an implantable cardiac monitor, pacemaker or defibrillator, dementia, inability to provide informed consent, and those with a medical illness with an anticipated life expectancy of <3 months.

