### Participant Consent and Enrollment

The research team will confirm the eligibility of interested individuals against the inclusion and exclusion criteria over the phone. Eligible individuals will be provided with participant information statements and consent information and given time to read the information. Research personnel will answer individuals’ questions. Participants will provide verbal consent to a member of the research team who will electronically sign off the consent form and keep the form in the secured university computer drive.

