### Data Collection

All study procedures have been designed to be conducted remotely using telephone or video calls. At baseline, we will obtain information on sociodemographics, self-reported weight and height, and concurrent medical conditions and medications and data to assess stroke risk, frailty, and activities of daily living. At the end of the program, we will conduct a usability survey of all participants via phone calls to obtain information related to their experiences with the screening program and obtain further information on any adverse events while participating in the program (Multimedia Appendix 1). All GPs who have patients enrolled in the study will be invited to provide their feedback in a survey (Multimedia Appendix 2). All electronic data and documents related to participants and the project will be securely stored in the university computer drive accessible by authorized research team members only.

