### Analysis

All analyses will be conducted according to the principle of intention-to-treat. Continuous variables will be presented as mean (SD) or median with IQR and categorical variables as frequency and percentage. The key outcomes, namely participant satisfaction in the AF screening program, usability of the screening program, and the incidence of new AF detected over 6 and 12 months, will be reported as frequency and percentages and will be compared between the intervention and control groups using the chi-square test. Comparisons between groups (intervention and control) for other outcomes will be assessed using the chi-square test or Fisher exact test for categorical variables and Student *t* test or Mann-Whitney test for continuous variables as appropriate. We will consider 2-tailed *P*<.05 as statistically significant. The agreement between the ECG device automatic algorithm and clinician interpretation will be evaluated using κ statistics. Subgroup analyses will be performed based on age, gender, and location. Subgroup analysis by frailty will be performed to examine the potential impact of frailty on the outcomes, feasibility, and acceptability of the program. The actual operational costs of delivering the project will be recorded and verified using invoices and receipts, including the costs of personnel involved in interpreting ECGs, which will be computed based on their hourly wages and the time they spent in their roles in this program. The resultant costs will be compared with the costs reported in the literature on the costs associated with the detection of AF in a similar older population. Missing data will be identified, and its causes will be described. Sensitivity analysis will be performed to examine the robustness of the findings [39].

Qualitative evaluation will be reported according to the COREQ (Consolidated Criteria for Reporting Qualitative Research) guidelines [40]. Interviews with patients and GPs will be thematically analyzed using an inductive approach [41]. Themes will be interpreted through the critical realism lens [37] and compared with the literature [42,43]. We will triangulate the quantitative and qualitative findings [44] from patient participants and GPs to acquire an in-depth understanding of the barriers to and enablers of implementing the screening program.

The process evaluation components [36], explanatory data, and anticipated outcomes are summarized in Table 2.

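### The trial is said to show AF incidence, but without a rhythm recording at entry the planned percentage is a yield of previously undiagnosed AF, prevalent plus incident

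*Protocol article*

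**What the plan says.** Two places in the Protocol article use the word incidence for the AF result.

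- Discussion, Anticipated Research Outcomes and Impacts on Clinical Practice and Policy: "It will also provide evidence of AF incidence in older people in Australia". The sentence after it links this to a possible national screening programme.
- Methods, Analysis: one of the key outcomes is "the incidence of new AF detected over 6 and 12 months, will be reported as frequency and percentages", compared between arms by the chi-square test.

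Elsewhere the same result is described as detection. The Abstract states: "The primary clinical outcome is the AF detection rate". Sample Size and Anticipated Strengths use the same term, and the Objective section speaks of ascertainment rates.

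On the state of participants at entry:

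- The only AF exclusion in Study Population is "previously confirmed diagnosis of AF".
- Participant Consent and Enrollment: "The research team will confirm the eligibility of interested individuals against the inclusion and exclusion criteria over the phone".
- Data Collection: "At baseline, we will obtain information on sociodemographics, self-reported weight and height, and concurrent medical conditions and medications", followed by stroke risk, frailty and activities of daily living. No ECG is listed.
- Anticipated Challenges and Limitations confirms that the baseline history is self-reported.
- The first study ECGs are those of the monitoring programme: after randomisation in the intervention arm, and after the 6-month wait in the control arm.

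Background reports that "1.4% of people aged ≥65 years were living with undiagnosed AF", from a review of cross-sectional studies.

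**The concern.** Incidence is the occurrence of new disease among people free of it at the start. This design excludes people who have been told they have AF, but not people who have it without knowing. Finding that second group is the purpose of the programme.

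As written, AF seen on a participant's first home trace counts as new AF in the same way as AF first seen months later after many normal traces. The article states no rule that separates them. The problem recurs at 12 months, because the control arm's first screening round falls after month 6 and adds its own previously undiagnosed cases to a figure that the Analysis section also calls incidence.

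At stake is a conclusion aimed at policy. If the percentage is read as the rate at which older Australians develop AF, it will be too high. A reader planning a programme also cannot tell how much of the yield a single recording would have captured.

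**Working it through.** **1. The plan's own figure.** Inputs from Sample Size: 10% versus 1% detection, 80% power, two-sided α 0.05; 1:1 allocation. Pooled-variance formula for two proportions, no continuity correction:

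n per arm = [z(0.975)·√(2·p̄·(1−p̄)) + z(0.80)·√(p1(1−p1) + p2(1−p2))]² / (p1 − p2)², with p̄ = 0.055

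= [1.960·√0.10395 + 0.842·√0.0999]² / 0.0081 = 99.5, rounded up to 100 per arm.

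The total is 200, as stated, and power at 100 per arm is 80.2%. The calculation concerns detection, so the incidence label does not alter it.

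**2. Expected AF at entry.** Input: 1.4% undiagnosed AF at age ≥65 (Background).

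- Intervention arm: 100 × 0.014 = 1.4 people. Both arms: 200 × 0.014 = 2.8 people.
- Chance of at least one in an arm of 100: 1 − 0.986^100 = 76%.

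**3. Share of the yield.** At the 10% design rate, 100 intervention participants give 10 detections. If screening finds every case present at entry, the share is 1.4 / 10 = 14%.

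**4. Effect of reading the yield as incidence.** On the same assumption:

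incident proportion = (10 − prevalent cases) / (100 − prevalent cases)

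| Undiagnosed AF at entry | Prevalent among 10 detections | Incident proportion | 10% overstates it by |
|---|---|---|---|
| 1.4% (Background, age ≥65) | 1.4 | 8.6 / 98.6 = 8.7% | 1.15 times |
| 3% (assumed) | 3 | 7 / 97 = 7.2% | 1.39 times |
| 5% (assumed) | 5 | 5 / 95 = 5.3% | 1.9 times |

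The article gives no prevalence for age ≥75. The last two rows only show the range.

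**5. Can the planned recordings separate the two kinds of case?** Only in part. All transmissions to the central monitor are logged (Textbox 1), so AF on the first trace can be identified. The traces last 30 seconds and are taken on weekdays (Intervention Group section). Paroxysmal AF already present at entry can be missed on early traces and caught later, so a first detection after a normal trace does not date the onset.

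**The case against.** The strongest reply is that the outcome is already defined as detection almost everywhere. Even the Analysis phrase refers to AF that was detected, reported as a percentage, and no person-time rate is planned. The population claim is one Discussion sentence that matches no objective, outcome or analysis. No test, estimate or sample size changes. This stands, and it limits the point to the label and the inference drawn from it. It does not rescue the Discussion sentence, which promises something the design as written does not deliver.

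It can also be said that the trial compares screening with usual care, not repeated with one-off recording, so the article need not specify a split by first trace. That is fair. The split is offered as a cheap descriptive addition, and its absence is not the fault.

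A reader might infer more than the document supports:

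- *That the randomised comparison is biased.* Undiagnosed AF is balanced between the arms in expectation, and finding it sooner is the effect under test.
- *That AF present at entry stays hidden in controls until month 6.* Controls have usual GP care, their AF is captured by confirmed self-report during the wait, and 1% control detection is assumed.
- *That the planned ECGs say nothing about timing.* The logs identify first-trace AF. What they cannot do is establish that later AF is incident.
- *That the share is well above 14%, from dividing 1.4% by the yield of a trial cited in Background.* For the 5.3% yield that gives 26%. That yield came from two 2-week patch recordings in people with hypertension, which is neither this trial's device nor its design rate.

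Multimedia Appendix 1 is not shown. Data Collection lists no baseline ECG, and the device is described as supplied when the monitoring programme begins.

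**Conclusion.** The point holds as a matter of labelling and inference. The percentage called incidence in Analysis, and offered as evidence of AF incidence in older Australians in the Discussion, is the yield of previously undiagnosed AF. At the article's own 1.4%, about 1.4 of 100 intervention participants would have AF at entry, or about 14% of detections at the 10% design rate.

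That size rests on three assumptions: the ≥65 figure applies to volunteers aged ≥75, screening finds every such case, and the 10% design rate is realised. A higher prevalence at ≥75 would raise the share.

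The 6-month comparison of detection and the total of 200 stand. The wording should still be corrected, because it supports a policy-facing statement and the change costs very little.

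**What to change.** - **Analysis:** replace the incidence wording with *new AF detected (yield of previously undiagnosed AF)*.
- **Discussion:** delete the incidence claim, or reword it to detection of previously undiagnosed AF among trial participants.
- **One descriptive table from the transmission logs already collected:** AF on the first interpretable trace, shown separately from AF first detected after at least one non-AF trace. Count from month 0 in the intervention arm and from month 6 in controls.
- **Limit on that table:** do not call the second group incident or give it a person-time incidence rate, because intermittent 30-second traces can miss paroxysmal AF that was present at entry.

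The cost is two wording changes and one small table with few cases per cell. No new data, visits or participants are needed.

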### Anticipated Challenges and Limitations

All study procedures have been designed to be conducted remotely by telephone or video interface to facilitate this study in the context of the COVID-19 pandemic. Therefore, the collection of baseline data and medical history relies on participants’ self-reported information. There is a potential for loss to follow-up in older patients who are frail; for example, participants do not record ECGs. We will attempt to minimize this by following up with patients when no ECG is received for 3 consecutive days. There may be a potential selection bias in this study based on the inclusion criteria. For example, this trial is limited to older people who can understand English and have a smartphone. These participants may come from higher socioeconomic communities and represent a more motivated cohort than the general population of older people.

### Conclusions

The findings from this implementation study will guide the development of practical and attainable solutions to address a gap in AF screening among older people in the community and other vulnerable groups. In addition, this study will explore the experiences and feedback from participants and clinicians and provide new knowledge on the processes involved in the implementation of the screening program and how processes can be improved, replicated, and scaled up to reach larger populations.

## Appendix

Multimedia Appendix 1 Patient participant data collection at baseline, 6-month follow-up, and 12-month completion of the program and semistructured interview guide.

Multimedia Appendix 2 General practitioner data form and semistructured interview guide.

## Abbreviations

AF: atrial fibrillation
CHADS-VASc: congestive heart failure, hypertension, age ≥75 (double score), diabetes, stroke (double score), vascular disease, age 65 to 74 and sex category
COREQ: Consolidated Criteria for Reporting Qualitative Research
ECG: electrocardiogram
FRAIL: Fatigue, Resistance, Ambulation, Illnesses, and Loss of Weight
GP: general practitioner
RCT: randomized controlled trial
REDCap: Research Electronic Data Capture
